**11.2.6. Visit 6 (Day 180+30 after vaccination) (only the immunity subgroup)**

(1) Blood collection

---

Blood collection for humoral immunogenicity test: about 5.0 mL venous blood is collected from the participant with a procoagulant tube (containing only procoagulant), and the serum is separated according to the operating procedures and sub-packaged into cryopreservation tubes.

(2) Safety observation

Collect SAE, AESI, and pregnancy events.

(3) COVID-19 case observation

Determine whether the participant presents with COVID-19-related signs or symptoms.

**11.2.7. Protective efficacy visits (from the day of vaccination to the 180th day after vaccination)**

The routine surveillance and case surveillance are carried out according to the procedure of 6.6 *observation of protective efficacy*.

**11.2.8. End of study**

The site closure report will be issued when the data entry in EDC is completed, the queries are resolved, the database is locked and all the materials are reviewed.

**11.3. Methods of observation of protective efficacy**

**11.3.1. routine monitoring**

7 days after booster vaccination in all subjects, the researchers were required to conduct the following "Routine monitoring" in the form of a combination of remote and on-site visits:

- Whether the subjects had COVID-19-related symptoms during the remote visit by the researchers;
- A throat swab sample a1(for SARS-CoV-2 nucleic acid or antigen detection) is

---

taken when the researcher is informed through a remote visit that the subject has one or more of the following conditions, at the same time further inquiry, record and guide the subject to continue observation, record the type of symptoms, starting and ending time, the severity of information; If an on-site interview is conducted (the on-site interview can be conducted by visiting the study site or by visiting the researcher), a nucleic acid throat swab B 1(backup) :

- ① any possible signs or symptoms of COVID-19(fever or chills, fatigue, headache, dry throat, muscle pain, sore throat, nasal congestion/runny nose, anorexia/nausea/vomiting, diarrhea, new onset of smell/taste disorder, conjunctivitis) ;
- ② any or more respiratory symptoms (cough, shortness of breath, or dyspnea), lasting at any time;
- ③ clinical or imaging evidence of pneumonia.

### **11.3.2. Case surveillance**

**If the test result for SARS-CoV-2 nucleic acid or antigen in the throat swab sample A1 of the subject is positive, the researcher needs to continue to carry out the following "case monitoring" work:**

- Send the throat swab sample B1 of the subject's nucleic acid (if collected) to the central laboratory for SARS-CoV-2 variant typing testing, guide and coordinate the subject to go to a designated hospital for chest imaging examination (chest CT);
- Provide necessary medical supplies to the subjects, continue to conduct remote visits twice a week, guide them to observe and record symptoms and self-medication at home, or guide them to seek medical treatment at designated hospitals according to the situation; If the subject has symptoms such as Tachypnea or dyspnea, guide and coordinate the subject to detect blood oxygen saturation according to the situation; According to the recovery of symptoms of the subjects, conduct on-site visits, collect samples of nucleic acid oropharyngeal swabs or antigen Nasopharyngeal swab for SARS-CoV-2 nucleic acid or antigen detection until the results of SARS-CoV-2 nucleic acid or antigen turn negative

---

or the symptoms disappear or stabilize according to the evaluation of the investigator;

- Collect the treatment status and medical history of the subjects to determine the severity of COVID-19, record the type of symptoms, occurrence time, reporting time, collection time, testing time, reporting time, diagnosis time, and outcome information of each nucleic acid sample, and form relevant records;
- Establish a COVID-19 case file for the subjects, fill out and report the first/follow-up COVID-19 case report based on remote visits;
- The on-site and medical monitoring teams need to conduct a preliminary review of the completeness, rationality, and logic of the COVID-19 case report, raise necessary questions and information supplement requirements, and submit it to the researchers for diagnosis and judgment.

**If the test result of the throat swab sample A1 for SARS-CoV-2 nucleic acid or antigen is negative, the following retesting work needs to be continued:**

- Within 48 hours, the throat swab sample A2 (for SARS-CoV-2 nucleic acid or antigen testing) and sample B2 (backup sample) need to be collected again;
- If the test result for SARS-CoV-2 nucleic acid or antigen in the throat swab sample A2 of the subject is positive, the relevant work shall be carried out according to the above case monitoring process;
- If the test result for SARS-CoV-2 nucleic acid or antigen in the throat swab sample A2 of the subject is still negative, the relevant work will continue according to the routine monitoring process mentioned above.

**Frequency and method of "visit":**

- Starting from 7 days after the booster vaccination, remote visits will be conducted twice a week (with a recommended interval of 2-3 days) until the 90th day after vaccination: (1) If the number of confirmed primary endpoint cases reaches 162, the visit video rate will be adjusted to once a month until the 180th day after vaccination; (2) If the number of confirmed primary endpoint cases does not

---

reach 162, remote visits will continue to be conducted twice a week until the number of primary endpoint cases reaches 162, and the video visit rate will be adjusted to once a month until the 180th day after vaccination;

- If the subject's SARS-CoV-2 nucleic acid or antigen test results are positive, regardless of the stage mentioned above, they will be visited twice a week (with a recommended interval of 2-3 days) until their nucleic acid or antigen test results turn negative or symptoms disappear or stabilize after evaluation by the researcher;
- Remote follow-up methods include text messages, phone calls, videos, and photos, and on-site visits are conducted based on the monitoring process and actual situation mentioned above.

#### **11.4. Safety observation method**

##### **11.4.1. Safety observation time and method**

###### **(1) Within 28 days after vaccination**

Participants will be observed at the vaccination site for 30 minutes after vaccination. Investigators who have been trained and authorized need to systematically observe and measure the body temperature of each participant 30 minutes after vaccination, and record all AEs within 30 minutes after vaccination in detail. AEs will be observed and recorded through the Diary Card from 0 to 14 days after vaccination, and AEs will be collected and recorded through the Contact Card from 15 to 28 days after vaccination.

Investigators should check the original safety information of the Diary Card and Contact Card in time and input it into EDC after checking. Investigators should verify the name, duration, and severity of any AE and evaluate and determine its relationship to vaccination. Measures taken in response to the AE, combined treatment, and outcome of the AE, whether the event was a serious adverse event, and whether the event led to study discontinuation, must also be documented.

---

## (2) Long-term safety observation

SAE, AESI, and pregnancy-related events should be collected and recorded for all participants 6 months after vaccination through a combination of remote visits and participant active reporting. SAE, AESI, and pregnancy-related events collected need to be followed up, recorded, and reported following SAE and pregnancy-related event reporting in this protocol.

### 11.4.2. Safety observation content and indicators

Routine safety observation content includes all solicitation and non-solicitation, as well as any medical events related to or unrelated to vaccination that occur during the clinical study observation period.

Injection site (local) AE: Pain, induration, redness, rash, swelling, pruritus, cellulitis.

Non-injection site (systemic) AE: fever (axillary temperature), diarrhea, nausea, vomiting, headache, myalgia (non-injection site), arthralgia, chills, anorexia, fatigue/asthenia, acute allergic reaction

Other events: any medical event other than the above, such as acute illness, accidental injury, etc.

### 11.4.3. Safety observation grading standards.

Adverse events at the injection site and non-injection site (Table 2 and Table 3) are judged regarding the Guidelines for Grading Criteria of Adverse Events in Clinical Trials of Preventive Vaccines issued by NMPA. For adverse events not mentioned in the grading table, the intensity will be assessed according to Table 4.

**Table 2 Grading of Injection Site (Local) Adverse Events**

| Symptoms/Signs | Grade 1                                    | Grade 2                          | Grade 3                       | Grade 4                             |
|----------------|--------------------------------------------|----------------------------------|-------------------------------|-------------------------------------|
| Pain           | No influence or mild influence on physical | Influence on physical activities | Influence on daily activities | Loss of basic self-care ability, or |

|                              | activities                                                                                                             |                                                                                                   |                                                                                                                                                                                            | hospitalization                                                  |
|------------------------------|------------------------------------------------------------------------------------------------------------------------|---------------------------------------------------------------------------------------------------|--------------------------------------------------------------------------------------------------------------------------------------------------------------------------------------------|------------------------------------------------------------------|
| Induration*,
Swelling** # | Diameter of 2.5 - < 5 cm or area of 6.25 - < 25 cm  and no influence or slight influence on daily living   | Diameter of 5 - < 10 cm or area of 25 - < 100 cm  or influence on daily living        | Diameter of $\geq 10$ cm or area of $\geq 100$ cm  or ulceration or secondary infection or phlebitis or aseptic abscess or wound drainage or serious influence on daily living | Abscess, exfoliative dermatitis, dermis, or deep tissue necrosis |
| Rash*,
redness** #        | Diameter of 2.5 - < 5 cm or area of 6.25 - < 25 cm  , and no influence or slight influence on daily living | Diameter of 5 - < 10 cm or area of 25 - < 100 cm  , or influence on daily living      | Diameter of $\geq 10$ cm or area of $\geq 100$ cm  or ulceration or secondary infection or phlebitis or aseptic abscess or wound drainage or serious influence on daily living | Abscess, exfoliative dermatitis, dermis, or deep tissue necrosis |
| Pruritus                     | Injection site pruritis, relieved spontaneously or within 48 h after treatment                                         | Injection site pruritis is not relieved within 48 h after treatment                               | Influence on daily living                                                                                                                                                                  | NA                                                               |
| Cellulitis                   | NA                                                                                                                     | Non-injection therapy indicated (e.g., oral anti-bacterial, anti-fungal, anti-viral drug therapy) | Intravenous injection therapy indicated (e.g., intravenous anti-bacterial, anti-fungal, antiviral drug therapy)                                                                            | Sepsis, tissue necrosis, etc.                                    |

Note: \*In addition to direct measurement of diameter for grading evaluation, changes in measurement results are also recorded.

\*\*Use the maximum measured diameter or area.

#Evaluation and grading of induration and swelling, rash, and redness are based on functional level and actual measurement results, the parameters with higher grades are selected.

**Table 3 Grading of (Systemic) AEs at Non-injection Site**

| Signs                                | Grade 1                                                                                                    | Grade 2                                                                                | Grade 3                                                                                                                                                 | Grade 4                                                                                      |
|--------------------------------------|------------------------------------------------------------------------------------------------------------|----------------------------------------------------------------------------------------|---------------------------------------------------------------------------------------------------------------------------------------------------------|----------------------------------------------------------------------------------------------|
| Fever
[axillary temperature (°C)] | 37.3~<38.0                                                                                                 | 38.0~<38.5                                                                             | 38.5~<39.5                                                                                                                                              | ≥ 39.5, lasts for longer than 3 days                                                         |
| Diarrhea                             | Slight or transient, 3-4 times/day, abnormal stool appearance, or slight diarrhea lasting less than 1 week | Moderate or persistent, 5-7 times/day, abnormal stool appearance, or diarrhea > 1 week | > 7 times/day, abnormal stool appearance, or bloody diarrhea, orthostatic hypotension, electrolyte imbalance, with > 2 L intravenous infusion indicated | Shock due to hypotension, requiring hospitalization                                          |
| Nausea                               | Transient (< 24 h) or intermittent and normal food intake                                           | Persistent nausea resulting in food intake decreased (24 - 48 h)                       | Persistent nausea resulting in almost no food intake (> 48 h) or intravenous fluids replacement required                                         | Life-threatening (e.g., hypotensive shock)                                                   |
| Vomiting                             | 1-2 times/24 h and no influence on activities                                                       | 3-5 times/24 h or limited activities                                            | > 6 times/24 h or intravenous fluids replacement required                                                                                        | Shock due to hypotension, requiring hospitalization or other routes of nutrition      |
| Anorexia                             | Decreased appetite, but no reduction in food intake                                                        | Decreased appetite, and decreased food intake, but no significant weight loss          | Decreased appetite, with significant weight loss                                                                                                        | Requiring intervention measures (such as intragastric tube feeding and parenteral nutrition) |

|                              |                                                           |                                                                                                     |                                                                                     |                                                                                  |
|------------------------------|-----------------------------------------------------------|-----------------------------------------------------------------------------------------------------|-------------------------------------------------------------------------------------|----------------------------------------------------------------------------------|
| Headache                     | No influence on daily activities, treatment not indicated | Transient, slight influence on daily activities, treatment, or intervention indicated possibly      | Serious influence on daily activities, treatment, or intervention indicated         | Stubborn, emergency treatment or hospitalization indicated                       |
| Myalgia (non-injection site) | No influence on daily activities                          | Slightly influence daily activities                                                                 | Severe muscle pains, seriously influence daily activities                           | Emergency treatment or hospitalization                                           |
| Arthralgia                   | Mild pain, without impairing function                     | Moderate pain; requiring analgesics and/or impairing function, but no influence on daily activities | Severe pain; requiring analgesics and/or influence on daily activities              | Disabling pain                                                                   |
| chill                        | A mild feeling of cold, teeth chattering                  | The whole body shivers moderately                                                                   | Severe/persistent tremor                                                            | Emergency treatment or hospitalization                                           |
| Fatigue, asthenia            | No influence on daily activities                          | Influence on normal daily activities                                                                | Serious influence on daily activities, unable to work                               | Emergency treatment or hospitalization                                           |
| Acute allergic reaction*     | Urticaria localized (blister), treatment not indicated    | Urticaria localized, treatment indicated or mild angioedema, treatment not indicated         | Extensive urticaria or angioedema, treatment indicated, or mild bronchospasm | Allergic shock or life-threatening bronchospasm or laryngeal edema |

\* refers to type I hypersensitivity.

Table 4 Grading of Other Adverse Events

|         |         |         |         |         |
|---------|---------|---------|---------|---------|
| Grade 1 | Grade 2 | Grade 3 | Grade 4 | Grade 5 |
|---------|---------|---------|---------|---------|

---

|                                                                                                   |                                                                                                                                    |                                                                                                                          |                                                                                           |       |
|---------------------------------------------------------------------------------------------------|------------------------------------------------------------------------------------------------------------------------------------|--------------------------------------------------------------------------------------------------------------------------|-------------------------------------------------------------------------------------------|-------|
| Mild: Short-term (< 48 h) or mild discomfort, no influence on activities, treatment not indicated | Moderate: mildly or moderately restricted activity, medical attention indicated possibly, no treatment or mild treatment indicated | Severe: significantly restricted activity, medical attention and treatment indicated, hospitalization indicated possibly | Critical: may be life-threatening, severely restricted activity, intensive care indicated | Death |
|---------------------------------------------------------------------------------------------------|------------------------------------------------------------------------------------------------------------------------------------|--------------------------------------------------------------------------------------------------------------------------|-------------------------------------------------------------------------------------------|-------|

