#### **6.2.2. Secondary endpoint(s)**

➤ Secondary endpoint(s) of protective efficacy

1)The person-year incidence rate of severe and critical COVID-19 cases (Appendix 1) occurring from 14 days after booster vaccination of the investigational vaccine or placebo in the adults aged 18 and older who have completed 2 or 3 doses of inactivated COVID-19 vaccines.

2)The person-year incidence rate of COVID-19 cases leading to death (Appendix 1) occurring from 14 days after booster vaccination of the investigational vaccine or placebo in adults aged 18 and older who have completed 2 or 3 doses of inactivated COVID-19 vaccines.

➤ Secondary endpoint(s) of immunogenicity

1)The geometric mean titer (GMT), geometric mean increase (GMI), and seroconversion rate (SCR) of SARS-CoV-2 virus neutralizing antibody against the main epidemic strains among the immunogenicity subgroup 7 days, 14 days, 28 days, 3 months and 6 months after booster vaccination of the investigational vaccine or placebo.

2)The geometric mean titer (GMT), geometric mean increase (GMI), and seroconversion rate (SCR) of SARS-CoV-2 S-protein IgG antibody against the main epidemic strains among the immunogenicity subgroup 7 days, 14 days, 28 days, 3 months and 6 months after booster vaccination of the investigational vaccine or placebo.

➤ Secondary endpoint(s) of safety

---

1)The incidence of AEs within 30 mins, 14 days, and 28 days after booster vaccination of the investigational vaccine or placebo in adults aged 18 and older who have completed 2 or 3 doses of inactivated COVID-19 vaccines.

2)The incidence of SAEs and AESIs within 6 months after booster vaccination of the investigational vaccine or placebo in adults aged 18 and older who have completed 2 or 3 doses of inactivated COVID-19 vaccines.

3)The pregnancy events (including the pregnancy outcome, the delivery characteristics, the condition of the newborn, and the growth and development within 1 month after birth) within 6 months after booster vaccination of the investigational vaccine or placebo in the adults aged 18 and older who have completed 2 or 3 doses of inactivated COVID-19 vaccines.

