#### **11.8.2.5. Safety Analysis**

---

MedDRA will be used for the medical coding of adverse events and serious adverse events, classified and counted according to the SOC and PT. The solicited adverse events for the reactogenic subgroup will be classified and counted according to the inoculation site and non-inoculation site (systemic) adverse events specified in the protocol. TEAE will be mainly analyzed in this study and the adverse events that occurred before vaccination will be listed in the form of a list. Unless otherwise specified, the following adverse events are TEAEs.

The frequency, number, and incidence of all adverse events and AESIs, adverse events and AESIs related to the study vaccine, adverse events and AESIs unrelated to the study vaccine, adverse events and AESIs of grade 3 or above, and adverse events and AESIs of grade 3 or above related to the study vaccine will be calculated respectively in the test group and control group. Fisher's precision probability test will be used to compare the differences between groups in the incidence of the above adverse events. The occurrence time and severity of adverse events will be statistically described. The adverse events and AESIs related to the study vaccine or unrelated to the study vaccine will be listed respectively.

The frequency, number, and incidence of all serious adverse events, serious adverse events related to the study vaccine, and serious adverse events not related to the study vaccine will be calculated respectively in the test group and control group. Fisher's precision probability test will be used to compare the differences between groups in the incidence of the above adverse events. The serious adverse events will be listed.

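### Table 3 gives no grade to a fever of 39.5 °C or more lasting 3 days or less, nor to six vomiting episodes in 24 h without another criterion, so the planned grade 3 or above comparison rests on an incomplete scale

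*Protocol*

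**What the plan says.** **Fever (section 11.4.3, Table 3).** The first three grades are adjoining axillary temperature bands with no duration condition: Grade 1 from 37.3 to below 38.0 °C, Grade 2 from 38.0 to below 38.5 °C, Grade 3 from 38.5 to below 39.5 °C. Grade 4 is "≥ 39.5, lasts for longer than 3 days".

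**Vomiting (same table).** Grade 1 is 1 to 2 episodes in 24 h with activities unaffected. Grade 2 is "3-5 times/24 h or limited activities" and Grade 3 is "> 6 times/24 h or intravenous fluids replacement required". Grade 4 rests on shock, hospitalization or another route of nutrition.

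**Rules around the tables.** Section 11.4.3 says that local and systemic events are judged with regard to the "Guidelines for Grading Criteria of Adverse Events in Clinical Trials of Preventive Vaccines issued by NMPA". It adds: "For adverse events not mentioned in the grading table, the intensity will be assessed according to Table 4". A note under Table 2 says that "the parameters with higher grades are selected", but it is confined to induration, swelling, rash and redness.

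**Use of the grades.** Section 11.8.2.5 calculates, by arm, the incidence of "adverse events and AESIs of grade 3 or above", overall and vaccine-related, and compares the arms with Fisher's test. The named safety endpoint in section 6.2.2 does not depend on grade: "The incidence of AEs within 30 mins, 14 days, and 28 days after booster vaccination".

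**The concern.** A severity scale should assign one grade to every value that can be recorded, and the grade should not become undefined as the event gets worse. The fever row fails at its upper end: 39.4 °C is Grade 3, and 39.6 °C for two days has no grade.

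Fever and vomiting are both listed systemic events in section 11.4.2, and section 4.2.1 names fever among the common events after vaccine injection. High fever is therefore part of what a grade 3 or above table is meant to show. If sites fill the gap in different ways, the by-arm count in section 11.8.2.5 depends partly on local habit. Section 6.12 also lists the severity of adverse reactions among the grounds for suspending or terminating the study, so the grades may be read during the trial as well as at its end.

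**Working it through.** No sample size, power or alpha figure is involved, and the plan states no figure to reproduce. The check is whether the cells cover all recordable values.

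**Fever.** The four cells were applied literally to temperatures from 37.3 to 42.0 °C in steps of 0.1 and to durations of 1 to 7 whole days, with the Grade 4 cell requiring both its conditions.

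- Temperatures: (42.0 − 37.3)/0.1 + 1 = 48. Combinations: 48 × 7 = 336.
- Ungraded: all temperatures from 39.5 to 42.0 °C, which is 26 values, at 1, 2 or 3 days: 26 × 3 = 78.
- The other 336 − 78 = 258 combinations receive exactly one grade.

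These counts describe cells of a grid, not participants. They show that the gap is a single block at the top of the scale.

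**Other reading of the comma.** If the comma in the Grade 4 cell meant *or*, a two-day fever of 40 °C would be Grade 4. A fever below 39.5 °C lasting more than 3 days would then also meet Grade 4 while sitting in a Grade 1, 2 or 3 band. That closes the gap but creates an overlap. Other cells of Table 3 write *or* where they mean it, so the joint condition is the more natural reading. The row needs clarification either way.

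**Vomiting.** Counts of 1 to 8 in 24 h were crossed with limited activities (yes/no) and intravenous fluids (yes/no), setting aside the Grade 4 criteria. The only ungraded combination is six episodes with neither feature:

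| Episodes in 24 h | Limited activities | Intravenous fluids | Grade(s) met |
|---|---|---|---|
| 6 | no | no | none |
| 6 | yes | no | 2 |
| 6 | no | yes | 3 |
| 6 | yes | yes | 2 and 3 |

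The diarrhea row of the same table has adjoining frequency bands (3–4, 5–7, more than 7), which suggests that the jump in the vomiting row is a slip.

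**Does another rule close the gaps?**

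1. Table 4 is reserved for events that the grading table does not mention. Fever and vomiting are mentioned.
2. The higher-grade note under Table 2 covers four local signs only. It also presupposes that at least one grade applies.
3. The NMPA guideline is cited, but its content is not in the protocol, and no sentence says what to do with an event that fits no cell.

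**Effect on the grade 3 or above count.** It depends on what the investigator does with a short fever of 39.5 °C or more:

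- Grade 3 or Grade 4 by judgement: the event is counted.
- Table 4, despite its wording: the grade turns on restriction of activity and need for care, so an event with moderate restriction could be Grade 2 and not counted.
- No grade recorded: whether it is counted is not stated.

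**The case against.** The strongest answer is that little or nothing need be lost. Section 11.4.1 requires the investigator to verify the severity of every adverse event, so some grade should be assigned. The cells on either side of the fever gap are Grades 3 and 4, and either choice keeps the event in the grade 3 or above count. On that view the practical effect is confusion between Grades 3 and 4. The governing standard is the NMPA guideline, which may resolve the gap; the protocol does not show whether the hole lies in the standard or arose in transcription or translation. Handling of ungraded events may also be covered in a statistical analysis plan that is not at hand.

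Much of this stands. A reader might infer that the most intense short fevers are excluded from a safety endpoint. The protocol does not support that: no sentence excludes an event that fits no cell, and grade 3 or above incidence is a planned analysis, not a named endpoint. A reader might also infer that six vomiting episodes never have a grade; that is true only when no other criterion in the row is met.

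What does not stand is that the table works as printed. An investigator applying it finds no grade, and the one written fallback does not apply. Consistent grading then relies on each investigator choosing the same way out, with no instruction to do so.

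**Conclusion.** The point holds as an incomplete grading rule. On its literal text, Table 3 assigns no grade to an axillary fever of 39.5 °C or more lasting 3 days or less, nor to exactly six vomiting episodes in 24 h with no other criterion met. The fever gap matters more, because it lies where grades feed the by-arm comparison in section 11.8.2.5. Those events may be graded inconsistently or left out. The primary efficacy analysis and the incidence of adverse events of any grade are untouched.

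The size cannot be computed from the protocol. As an illustration only, an assumed rate of 0.5% to 3% for fever of 39.5 °C or more gives 0.005 × 1,600 = 8 to 0.03 × 1,600 = 48 vaccine recipients. A reader might take that as the number lost. It is not: it includes fevers lasting more than 3 days, which are Grade 4, and those that an investigator grades 3 or 4 anyway.

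The direction is also not established. With a saline comparator it is plausible that high fevers soon after injection are more frequent in the vaccine arm, so that missing grades would understate the difference. But fever is also a COVID-19 symptom in Appendix 1, and both arms can contribute.

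The conclusion assumes that the Grade 4 fever cell requires both conditions. If it does not, the gap becomes an overlap and the row still needs correcting.

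**What to change.** Reconcile the fever and vomiting rows of Table 3 with the cited NMPA guideline. The result should meet three requirements: the bands adjoin; every recorded temperature and duration, and every vomiting count with its accompanying features, maps to exactly one grade; and severity does not fall as temperature rises. The cut-offs should come from that reconciliation, and none is proposed here. State whether the Grade 4 fever conditions apply jointly, and which grade applies when an event meets two.

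Align the grading check in the data capture system with the corrected rows. Regrade events already recorded while still blind, before database lock; section 6.11.5 allows unblinding only after lock, so the sequence is available. Regrading fever needs the recorded temperature and dates. Regrading vomiting needs the episode count, which the protocol does not show to be captured on the diary card, so that should be confirmed first.

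The cost is a change to two table rows, one system check and a limited blind regrade. The grade 3 or above rate may become slightly less favourable.
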